## Abstract

**Background:**

Tunnel anastomosis is a novel anastomotic technique for digestive tract reconstruction following proximal gastrectomy. A previous retrospective study by our team demonstrated its favorable antireflux effect; therefore, we hypothesize that tunnel anastomosis is noninferior to double-tract jejunal interposition reconstruction in preventing postoperative reflux esophagitis, and we will conduct this prospective study to further validate this assumption.

**Objective:**

In this study, we will prospectively compare tunnel anastomosis with the currently more prevalent double-tract jejunal interposition reconstruction technique to further validate its safety and efficacy.

**Methods:**

This is a multicenter prospective randomized controlled study that will enroll 240 patients who will undergo proximal gastrectomy. The study will be divided into 2 groups: the tunnel anastomosis group and the double-tract jejunal interposition reconstruction group, with 120 patients in each group. Patients will undergo clinical assessments and complete questionnaires preoperatively, as well as at the 3rd, 6th, and 12th months postoperatively. The primary end point is the incidence of reflux esophagitis within 1 year. The secondary end points include perioperative safety, postoperative quality of life, and postoperative nutritional status.

**Results:**

Recruitment of patients commenced in March 2022 and is scheduled to conclude in February 2027. The follow-up for all enrolled patients will be completed by February 2028.

**Conclusions:**

To our knowledge, this is the first prospective study on this technique, aiming to provide novel insights into the methods of digestive reconstruction following proximal gastrectomy.

## Introduction

Gastric cancer is a type of cancer with high morbidity and mortality in China, and the incidence of proximal gastric cancer is currently increasing [1-3]. Surgical treatment for proximal gastric cancer involves either total gastrectomy or proximal gastrectomy. Research has shown that proximal gastrectomy has the same therapeutic potential and efficacy as total gastrectomy, with advantages in terms of postoperative weight loss, dumping syndrome, anemia, and nutritional supplementation [4-10]. However, the issue of reflux esophagitis following proximal gastrectomy remains a significant challenge for surgeons [11]. Numerous studies have been conducted on antireflux techniques for digestive reconstruction, including double-tract jejunal interposition reconstruction and the double-flap technique (Kamikawa anastomosis), which have exhibited promising antireflux effects. Nevertheless, there is still no consensus on which reconstruction method should be considered the standard [12-17].

Tunnel anastomosis is a novel technique for digestive tract reconstruction following proximal gastrectomy. Owing to its preservation of an intact muscular flap, it ensures superior blood supply to the anastomotic site. A previous study by our team demonstrated that the antireflux effects of this technique are favorable [18]. Double-tract jejunal interposition reconstruction is currently the mainstream method for digestive tract reconstruction following proximal gastrectomy and is widely recognized by most experts [19]. The incidence of postoperative reflux esophagitis following this procedure is approximately 10%. Therefore, we selected this technique as the control group to further validate the effectiveness of TA.

We hypothesize that tunnel anastomosis is noninferior to double-tract jejunal interposition reconstruction in preventing postoperative reflux esophagitis. The objective of this study is to further validate the surgical safety and antireflux effect of tunnel anastomosis and assess the efficacy and ability of this technique to improve the quality of life of patients following proximal gastrectomy. It is hoped that this research will contribute to enhancing the theoretical and clinical practice foundations for refining surgical treatment strategies for upper gastric cancer.

## Methods

### Ethical Considerations

This study has been approved by the ethics committee of the Affiliated Cancer Hospital of Nanjing Medical University (2021-091-01). All patients will be fully informed of the precautions by a professional physician and provided with a written informed consent form before participation. All research information will be kept strictly at the study site and these data will be anonymized. This information will not be published outside the research without the consent of the patients.

### Study Design and Participants

This multicenter prospective study will be conducted at the Affiliated Cancer Hospital of Nanjing Medical University, First Affiliated Hospital of Nanjing Medical University, Affiliated Drum Tower Hospital of Nanjing University Medical School, First Affiliated Hospital of Soochow University, Affiliated Hospital of Nanjing University of Chinese Medicine, and Affiliated Gaochun Hospital of Jiangsu University. Figure 1 illustrates the flow of the study.

The inclusion criteria for this study are as follows: (1) age range of 18 to 80 years, with no sex preference; (2) histopathological confirmation of adenocarcinoma via endoscopic biopsy; (3) tumor located in the upper third of the stomach without esophageal involvement, largest diameter of ≤4 cm, and preoperative clinical stage cT1-4aN0M0; (4) Eastern Cooperative Oncology Group Performance Status score of 0 to 1; (5) no surgical contraindications identified through comprehensive preoperative evaluations; and (6) voluntary and informed consent signed by the patient or their legal representative. The exclusion criteria are as follows: (1) pregnant or lactating women; (2) presence of severe psychiatric disorders; (3) intraoperative findings indicating tumor invasion into the esophagus or unsuitability for proximal gastrectomy as determined by the primary surgeon; (4) preoperative or intraoperative discovery of distant organ metastasis or extensive peritoneal implantation metastasis; (5) presence of concurrent or metachronous malignancies, including other organ tumors; (6) incomplete radical surgery, including patients who underwent palliative tumor resection; (7) a history of gastrointestinal surgery; (8) a history of neoadjuvant radiotherapy or chemotherapy; (9) serious concomitant diseases that may make the survival period <5 years; and (10) cases considered unsuitable by the investigator.

**Figure 1. F1:**
[figure not shown]
Flow diagram for the study.

### Postrecruitment Withdrawals and Exclusions

Patients can withdraw from this study at any time. For patients who withdraw, the information collected before withdrawal will be used for the final analysis unless they request that their information be deleted.

### Preoperative Clinical Staging

Before surgery, all patients will be required to undergo an endoscopic examination with biopsy, endoscopic ultrasonography, a plain scan and a contrast-enhanced scan of the whole abdomen, and an upper gastrointestinal series. This comprehensive assessment aims to evaluate the gastric cancer lesion and abdominal lymph nodes thoroughly, with the objective of obtaining an accurate preoperative clinical diagnosis and tumor staging.

### Randomization

Patients can only be randomized into different groups once they have signed the informed consent form, completed baseline assessments, and been confirmed as fully meeting the inclusion criteria. Eligible patients will be randomly assigned to 1 of the following 2 groups at a 1:1 ratio: the tunnel anastomosis group or the double-tract jejunal interposition reconstruction group. The randomization process will use a stratified block randomization method, with disease stage (categorized as early stage or advanced stage) serving as the stratification factor. Patient group assignment will be determined based on random numbers generated by the R software program (version 4.0.2; R Foundation for Statistical Computing).

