### Power and Sample Size

This study is designed as a prospective randomized controlled trial with a noninferiority objective. It comprises 2 groups: the experimental group (tunnel anastomosis group) and the control group (double-tract jejunal interposition reconstruction group).

The reported incidence of reflux esophagitis for DTJIR in the literature varies widely, ranging from 1.7% to 25%. However, most contemporary studies report rates concentrated at approximately 10% [22-24]. On the basis of retrospective data from our center, the incidence of reflux esophagitis for TA is approximately 5%. Therefore, the estimated incidence of reflux esophagitis was 10% in the DTJIR group and 5% in the TA group. With a significance level set at α=.025 (one sided), a power of 1 – β of 0.80, a noninferiority margin of 0.05 (given the reported incidence of reflux esophagitis with the current surgical options, a noninferiority margin of ≤5% was deemed clinically acceptable as such a difference would not offset the significant benefits associated with the new technique), a 1:1 ratio between the experimental and control groups, and an anticipated dropout rate of 10%, the sample size was calculated via the PASS software (NCSS, LLC). The resulting sample sizes for both groups were 120 patients each.

Therefore, a total of 240 patients will be included in this study, with 120 patients in the experimental group and 120 patients in the control group.

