### Statistical Analysis

Data analysis will be conducted by professional statisticians. In addition to the overall comparative analysis conducted between the TA and DTJIR groups, we will further perform subgroup analyses stratified by disease stage and surgical approach.

Intention-to-treat and per-protocol approaches will be applied for efficacy analysis. An as-treated approach will be used for safety analysis. For continuous variables, a normality test will be performed first. For those that conform to a normal distribution, the 2-tailed *t* test will be used for statistical analysis (all continuous values will be expressed as means and SDs). Those not conforming to a normal distribution will be presented as quartiles and rank means, and the Mann-Whitney *U* test will be used to calculate the *P* value to compare differences between groups. For categorical variables, the chi-square test will be used for statistical analysis. Repeated-measure data will be analyzed using a mixed-effects model. Subgroup analyses will be conducted by disease stage (early vs advanced); surgical approach (open, laparoscopic, or robot-assisted); age; macroscopic types; and tumor, node, metastasis stage. All *P* values calculated in the analysis will be 2-sided, and *P*<.05 will be considered statistically significant. If missing data constitute more than 5%, multiple imputations will be conducted. Statistical analyses will be performed via SPSS (IBM Corp), Prism (GraphPad Software), or PASS.

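### Randomization is stratified by disease stage but the stated overall tests ignore it: a small, conservative loss that a stage-stratified risk difference would remove

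*Protocol article*

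**What the plan says.** Protocol article, Randomization: "The randomization process will use a stratified block randomization method", "with disease stage (categorized as early stage or advanced stage) serving as the stratification factor". No other factor is named.

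Protocol article, Statistical Analysis, on the overall comparison:

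- Categorical variables, which include the primary end point: "For categorical variables, the chi-square test will be used for statistical analysis".
- Normally distributed continuous variables: "the 2-tailed *t* test will be used for statistical analysis"; otherwise the Mann-Whitney test.
- Outcomes measured more than once: "Repeated-measure data will be analyzed using a mixed-effects model". Its covariates are not given.
- Stage enters only beyond the overall comparison: "we will further perform subgroup analyses stratified by disease stage and surgical approach".

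Study Design and Participants lists six hospitals. Centre appears neither in the randomization nor in the analysis.

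**The concern.** Stratified blocks hold the early-to-advanced mix nearly equal in the two arms. Differences between stages therefore contribute almost nothing to the true sampling variation of the treatment difference. An unstratified test still counts them in its variance. When stage is prognostic, the calculated standard error exceeds the true one, the interval is wider than it need be, and a noninferiority conclusion is slightly harder to reach.

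The same applies to secondary outcomes measured once, such as duration of surgery and blood loss, which get the plain t or Mann-Whitney test. Under Surgical Procedure, the extent of lymph node dissection depends on clinical stage (cT1N0 against the rest), so stage may well be related to these outcomes.

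This concerns a method the article states, not a detail left to an unseen analysis plan.

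**Working it through.** **Inputs from the article (Power and Sample Size):** 10% control, 5% tunnel anastomosis, margin 0.05, one-sided alpha 0.025, power 0.80, 1:1 allocation, 10% dropout.

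**Step 1. The plan's own figure.** The outcome is adverse, so the distance to the margin is 0.05 + 0.05 = 0.10.

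n = (0.10 × 0.90 + 0.05 × 0.95) × (1.960 + 0.842)² / 0.10² = 0.1375 × 7.85 / 0.01 ≈ 108 per arm, and 108 / 0.90 = 120. The stated size reproduces exactly, on the unstratified variance.

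Unstratified SE = √(0.1375 / 108) = 0.03568; 95% half-width = 1.96 × 0.03568 = 7.0 points.

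**Step 2. Variance that stage removes (assumed).** The article gives no rates by stage. I assume a stage odds ratio from 1 to 4 and an advanced share w from 30% to 70%, keeping the overall rates at 10% and 5%. In each arm the between-stage variance is w(1 − w)(p_adv − p_early)².

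Largest case (w = 0.30, odds ratio 4; control 5.8% and 19.8%, tunnel 2.8% and 10.2%):

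- Between-stage variance: 0.21 × 0.140² + 0.21 × 0.074² = 0.00412 + 0.00115 = 0.00527.
- Variance ratio: r = 1 − 0.00527 / 0.1375 = 0.9617.
- Unstratified SE relative to true SE: 1 / √0.9617 = 1.0197.
- Actual one-sided alpha (using this r): 1 − Φ(1.96 / √0.9617) = 0.0228.
- True SE: 0.03568 × √0.9617 = 0.03499. Power of a stratified test: Φ(0.10 / 0.03499 − 1.96) = 81.5%.

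| Advanced share | Odds ratio | r | SE excess | One-sided alpha | Power, stratified |
|---|---|---|---|---|---|
| any | 1 | 1.0000 | 0.0% | 0.0250 | 80.0% |
| 30% | 2 | 0.9910 | 0.5% | 0.0245 | 80.4% |
| 30% | 4 | 0.9617 | 2.0% | 0.0228 | 81.5% |
| 50% | 2 | 0.9915 | 0.4% | 0.0245 | 80.4% |
| 50% | 4 | 0.9712 | 1.5% | 0.0234 | 81.2% |
| 70% | 4 | 0.9835 | 0.8% | 0.0241 | 80.7% |

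The gain of 1.5 points is measured from the planned 80.0%. In that same case the unstratified test also benefits from the smaller true SE: Φ((0.10 − 1.96 × 0.03568) / 0.03499) = Φ(0.859) = 80.5%. The gap between the two tests is then about 1 point, so 1.5 is an upper limit.

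**Step 3. Simulation.** 216 evaluable patients, equal stages, blocks of 4, six equal centres, 3000 runs per scenario; stage odds ratio 1 to 4, centre SD 0 to 1.0 on the logit scale (assumed). The adjusted analyses are Mantel-Haenszel risk differences.

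| Scenario (10% v 5%) | Unadjusted | By stage | By stage and centre |
|---|---|---|---|
| No stage or centre effect | 81.4% | 81.2% | 79.6% |
| Odds ratio 4, centre SD 1.0 | 82.5% | 83.0% | 83.4% |

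At the margin (10% v 15%), rejection was 0.0233 to 0.0270 unadjusted and 0.0233 to 0.0273 by stage. The Monte Carlo SE is √(0.025 × 0.975 / 3000) = 0.0029, so neither differs detectably from 0.025.

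**Step 4. Continuous outcomes measured once (assumed).** If stage explains a share R² of the variance, the t-test SE is too large by a factor 1 / √(1 − R²), and the actual two-sided alpha is 2(1 − Φ(1.96 / √(1 − R²))).

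| R² | SE excess | Two-sided alpha |
|---|---|---|
| 2% | 1.0% | 0.048 |
| 5% | 2.6% | 0.044 |
| 10% | 5.4% | 0.039 |
| 20% | 11.8% | 0.028 |

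**The case against.** The strongest reply is that nothing here is invalid. The unstratified test is at worst slightly conservative, the sample size was computed on that same variance, and the planned 80% power is kept. In the largest case the half-width falls from 7.0 to 1.96 × 0.03499 = 6.9 points. Nothing in the article shows that stage predicts reflux esophagitis, and covariates are often left to the analysis plan. All of this stands, and it makes the point minor. It does not remove it, because the article names the tests, and they leave out the factor used to randomize.

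Stronger readings that the article does not support:

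- **That the error rate is inflated or the trial's chance of success materially cut.** The calculations show the opposite direction for alpha, and at most about 1.5 points of power.
- **That leaving out centre is a second mismatch.** Centre is not a randomization factor, so the unadjusted SE does not contradict the design on that account.
- **That the 1.7% to 25% range shows how far these hospitals differ.** Power and Sample Size gives it as the spread of published control rates and adds that most contemporary reports lie near 10%. Spreading six centres over it (1.7, 5, 8, 10, 15 and 25%) is an extreme assumption. Even then the between-centre variance is 0.00574 of 0.0962. The resulting imbalance SD of √(4 × 0.00574 / 216) = 1.0 point is already inside the unadjusted SE of √(4 × 0.0962 / 216) = 4.2 points. Removing centre entirely gives 4.1.
- **That adjusting for centre can only help.** About 216 × 0.075 = 16 events are expected over 12 stage-by-centre cells. Full adjustment moved simulated power by about −1.7 to +0.9 points against unadjusted.
- **That every comparison is a plain chi-square or t test.** Nutrition and quality of life at 3, 6 and 12 months are repeated measures and fall under the mixed-effects model, whose covariates are not stated.

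**Conclusion.** The point holds for stage and is of minor severity. Randomization is stratified by stage and the stated overall tests are not. For the primary end point the SE is 0% to 2.0% too large and at most about 1.5 points of power are at stake, with no inflation of type I error. This rests on assumed odds ratios of 1 to 4 and an advanced share of 30% to 70%; if stage does not predict reflux esophagitis, the effect is nil. For operating time, blood loss and other continuous outcomes measured once, an assumed R² of 2% to 20% gives an SE excess of 1.0% to 11.8%. The link between stage and extent of dissection makes some association plausible there, but the article does not quantify it. No finding about centre follows.

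**What to change.** For the primary end point, replace the chi-square test with a risk difference stratified by the stage category used at randomization (for example Mantel-Haenszel or stratified Miettinen-Nurminen). Compare its two-sided 95% confidence interval with the 0.05 margin. This also puts the result on the scale on which the margin is defined.

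Include stage as a covariate in the models for continuous and repeated-measure outcomes, and keep the stage subgroup analyses as they are.

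Adjustment for centre, with small centres pooled, may be added as an optional supportive analysis. It should not be the primary one.

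The cost is wording only. Stage is already known at randomization, and the 120 per group does not change. In the simulation, stratifying by stage cost 0.2 points of power when stage had no effect and gained 0.5 when the effects were strong. The change should be fixed before outcome data are analysed; follow-up is scheduled to end in February 2028.

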### Surgical Procedure

#### Overview

Both groups will undergo proximal gastrectomy with radical lymph node dissection (open, laparoscopic, or robot-assisted). cT1N0 patients will undergo D1+ lymph node dissection (1, 2, 3a, 4sa, 4sb, 7, 8a, 9, and 11p), whereas the remaining patients will undergo D2 lymph node dissection (D1+ and 11d). The surgeon will be required to hold the qualification of a chief physician and strictly adhere to the protocol procedures for reconstruction. All surgical procedures will be video or photo recorded.

#### Tunnel Anastomosis Technique

First, a linear cutting stapler will be used to transect the esophagus and create a gastric tube. Second, a 3-cm transverse incision will be made in the anterior wall of the remnant stomach, approximately 3 to 4 cm from the upper edge between the greater and lesser curvatures, reaching but not incising the muscular layer. Third, another parallel incision of equal length 3.5 cm distal to the first incision will be made. Fourth, between these 2 incisions, the connective tissue between the submucosa and muscular layers will be dissected via an electrosurgical knife, creating a tunnel flap of approximately 3 × 3.5 cm. Fifth, the posterior wall of the esophagus, located 5 cm from the residual stump, will be sutured with 4 stitches to the gastric wall at the upper edge of the seromuscular flap. Sixth, the esophageal stump will be pulled through the tunnel, and the anterior wall of the esophagus will be sutured with 4 to 5 stitches to the upper edge of the gastric seromuscular flap. Seventh, the submucosa and mucosal layers of the stomach will be incised at the lower incision of the tunnel to prepare for anastomosis with a caliber of 3 cm. Eighth, the esophageal stump will be opened using an ultrasonic knife, and the posterior wall of the esophagus will be sutured to the gastric mucosa and submucosa. Ninth, the anterior wall of the esophagus will be sutured to the full layer of the stomach. Finally, the lower edge of the seromuscular flap and the seromuscular layer of the remnant stomach will be sutured (Figure 2) [18].

**Figure 2. F2:**
[figure not shown]
Surgical steps for tunnel anastomosis.

#### Double-Tract Jejunal Interposition Reconstruction Technique

First, mesenteric vessels will be ligated 15 to 20 cm from the Treitz ligament. Second, the distal jejunum will be pulled anterior to the transverse colon and anastomosed with the esophagus. Third, approximately 10 to 15 cm below the esophagojejunal anastomosis, the distal jejunum will be anastomosed with the anterior wall of the remnant stomach. A 6-cm linear stapler will be used to create an anastomosis with a size of 4 cm. Subsequently, at 30 to 35 cm from the gastrojejunal anastomosis, a second anastomosis will be performed between the proximal and distal jejunum.

### Follow-Up

Follow-up will be conducted by dedicated follow-up staff. All patients will undergo follow-up visits at 3 months, 6 months, and 1 year postoperatively. At these visits, hematological examinations and postoperative quality of life assessments (using the European Organisation for Research and Treatment of Cancer Quality of Life Questionnaire Core 30 [EORTC QLQ-C30] and 36-Item Short Form Health Survey) will be performed. Nutritional status will be assessed based on hematological test results, changes in body weight, and the prognostic nutritional index (PNI). In addition, reflux symptoms will be assessed via the Visick score. At the 1-year follow-up, gastroscopy will be performed to assess reflux esophagitis according to the Los Angeles (LA) classification.

### Assessment of Outcomes

#### Primary End Points

The primary end point is the incidence of reflux esophagitis, which will be determined via gastroscopy results 1 year postoperatively. To determine the severity of reflux esophagitis, the modified LA classification system for reflux esophagitis will be used, which is considered a reliable method for categorizing reflux esophagitis. The modified LA classification criteria are as follows [20]:

Grade N—normal mucosaGrade M—minimal changes to the mucosa, such as erythema and/or whitish turbidityGrade A—nonconfluent mucosal breaks of <5 mm in lengthGrade B—nonconfluent mucosal breaks of >5 mm in lengthGrade C—confluent mucosal breaks <75% circumferentialGrade D—confluent mucosal breaks >75% circumferential

